### 7.2.3 *Run charts*

Run charts (or statistical process control [SPC] charts) will be developed to assess the impact of the potential novelty imposed by having the POC testing device, any teething difficulties, changes in work process and the Hawthorne effect from being in a study by tracking risk assessment behaviour in the practices. At the end of the study run charts of monthly CVD risk assessments counts for all of the practices will be generated for the duration of the study and for the 12 months prior. Special cause variation (statistically significant shifts in practice) occurring during that time and their association with PHO or the study will be determined using the standard Shewhart criteria.

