### 3. Background

#### 3.1 CVD risk assessment

Cardiovascular diseases (CVD) are readily preventable long term conditions that contribute to major ethnic and socioeconomic disparities in New Zealand. Interventions are available that could halve cardiovascular events (such as myocardial infarction and stroke) but the magnitude of treatment benefit is directly proportional to the magnitude of pre-treatment absolute CVD risk.

New Zealand CVD management guidelines recommend identifying people at high risk of developing CVD using a modified version of the Framingham risk prediction equation. Screening is recommended for all men over 45 years, all women over 55 years and 10 years earlier for people who are of Māori (indigenous New Zealanders), Pacific or South Asian ethnic groups, or people with known CVD risk factors. The intensity of management is then tailored according to a patient's five-year CVD risk.

Recently, new CVD and diabetes health targets for healthcare organizations have been introduced by the New Zealand Ministry of Health (MoH).a From January 2012 the Ministry will measure the number of completed CVD risk assessments for all eligible persons within the last five years (including diabetes checks). Data will be sourced from the Primary Health Organisation (PHO) performance programme. To assist District Health Boards (DHBs) in achieving the target of 90%, interim targets have been set over the next two years. The first is 60% by 1 July 2012, then 75% by 1 July 2013, and full achievement of the national target of 90% by 1 July 2014. PHOs and their member general practitioners (GPs) are well-informed of these targets via a number of mechanisms. These include PHO performance being annually benchmarked against others, PHOs receiving incentive payments (albeit modest) according to CVD risk assessment performance and planned PHO activities encouraging practice compliance such as CME/CNE and other practice interventions (such as visiting facilitators).

Up to 2011, we estimated that only about one third of the eligible population from the combined Northland and Auckland regions had been risk assessed and this was mainly via opportunistic screening. However, in the last 18 months there has been a marked acceleration of CVD risk assessment activity with some PHOs reporting 60%-70% screening of their eligible population.

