## 6.11 Practice follow-up

Each of the ten practices allocated to the POC group will undergo a training session in the use of the Cobas b 101 device. About half way through the study e.g. at 3 months, and at the end of the study practices will be contacted by PHO facilitators to document any additional staff time and/or other resources required by the use of the Cobas b 101 device and to assess its overall acceptability, feasibility and practice impact. The study will be continued until at least 1000 risk assessment have been performed and all the point of care consumables have been utilised by the POC group. It is estimated therefore the study duration will be in the order of 3-6 months.

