## 7. Statistical Considerations

### 7.1 Sample size

The study will involve a two-arm parallel cluster randomised controlled trial (CRCT) design with 20 practices (10 practices per arm). The primary outcome is whether the eligible patients have had a completed CVD risk assessment during the study. Preliminary analyses indicated that at least 70% of the enrolled populations within Manaia and Te Tai Tokerau PHOs have had a completed CVD risk assessment since 2006. Many of these people will be due for repeat CVD risk assessment. Significant delays to the conduct of this trial have occurred both prior to commencement and having to halt the trial due to manufacturing problems of the HbA1c discs. During this time practices have accelerated their CVD risk assessments in order to meet the national target (by July 2014 that 90% of the eligible population have had a CVD risk assessment in the previous 5 years.) As at April 2014, the two PHOs have screened approximately 80% of their eligible enrolled populations over the last five years. Therefore this trial now needs to adopt **a priori a non-inferiority hypothesis**.

Our previous sample size calculations May 2013, were as follows; We assumed a primary event rate of 70% in the laboratory group and a 10-15% increase to 85% in the POC group. This figure is based on a study set in community pharmacies where POC testing for cholesterol risk management led to a 10% increase. Taking into account an intraclass correlation coefficient of 0.025 as suggested by Elley et al (2005) from three New Zealand CRCTs; a 5% two-sided level of significant test and study power of 90%, we estimate a minimum sample size of 1000 risk assessments is needed (on average 50 patients per practice).

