### Key milestones

| Date           | Milestone                                                                                   |
|----------------|---------------------------------------------------------------------------------------------|
| May 2013       | Ethics submitted                                                                            |
| June 2013      | Ethics approval                                                                             |
| July 2013      | Recruit practices                                                                           |
| August 2013    | Start of study                                                                              |
| August 2013    | Study halted due to manufacturing problems cobas b 1010 discs                               |
| May 2014       | Study recommenced after re-validation cobas discs, retraining practices and Ethics approval |
| June 2015      | Estimated end of study                                                                      |
| September 2015 | Analysis complete.                                                                          |
| November 2015  | Paper submitted.                                                                            |

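### Section 7.2.3 uses Shewhart criteria to decide whether a shift is associated with the study or the PHO, but they can only detect the shift

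*Protocol*

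**What the plan says.** Section 7.2.3 gives the charts a purpose beyond display. They are to assess novelty of the device, teething difficulties, changes in work process and "the Hawthorne effect from being in a study by tracking risk assessment behaviour in the practices". The data are fixed: "run charts of monthly CVD risk assessments counts for all of the practices will be generated for the duration of the study and for the" preceding 12 months. The inference is fixed too. "Special cause variation (statistically significant shifts in practice) occurring during that time" is to be identified, and "their association with PHO or the study will be determined using the standard Shewhart criteria". One rule is therefore named for two tasks: finding a shift and linking it to the study or the PHO.

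The setting is a "cluster randomised controlled trial (CRCT) design with 20 practices (10 practices per arm") (section 7.1). Section 3.1 gives a timetable ending in "full achievement of the national target of 90% by 1 July 2014", and section 7.1 says that practices had accelerated their assessments to meet it. The key milestones in Appendix 5 put the restart in May 2014 ("Study recommenced after re-validation cobas discs, retraining practices and Ethics approval") and the estimated end in June 2015. Section 6.11 still says "It is estimated therefore the study duration will be in the order of 3-6 months".

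The treatment effect is analysed separately in section 7.2.2, by GEE or mixed models.

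**The concern.** A Shewhart signal rejects one hypothesis: that this series is still varying around its earlier level within its earlier limits. Association with the study is a different question. For the device, it asks whether POC practices changed differently from laboratory practices over the same months. For the PHO, it asks whether practices in one PHO changed differently from those in the other. No Shewhart rule contains a term for either.

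This is not detail that the protocol has left to the statistical analysis plan. The protocol names the method, and the method does not answer the question put to it.

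What is at stake is the interpretation of the charts. With many series and months, some signals will appear by chance, and the text describes signals as statistically significant. A system-wide influence such as the national target would also move practices in both arms. The laboratory practices that could separate these explanations are charted, but section 7.2.3 specifies no comparison with them.

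**Working it through.** The plan states no figure for the charts, so there is none to reproduce. The check is how often signals would appear without a device effect.

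**Inputs from the protocol.** There are 20 practices, 10 per arm, and 12 prior months. The study period is 3-6 months (section 6.11), or about 13 months from May 2014 to June 2015 (Appendix 5). Charts then have up to 12 + 6 = 18 or 12 + 13 = 25 points.

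**Assumptions, because the protocol does not state them.** There is one chart per practice, months are independent, and limits come from the 12 baseline months. Chart type, rule set and monthly count are also assumed. For the count, 50 assessments over about 5 months is 10 a month. The disc supply in section 10.1 (198 boxes of 10 for 10 practices) is nominally 198 tests per POC practice. That is 198/6 = 33 to 198/3 = 66 a month over 3-6 months, or about 15 over 13 months.

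**Step 1: no change, ideal known limits, 3-sigma rule only.** The false alarm rate is 0.0027 per point.
- 10 practices, 6 months: 1 - (1 - 0.0027)^60 = 15%.
- 20 practices, 6 months: 1 - (1 - 0.0027)^120 = 28%.
- 20 practices, 13 months: 1 - (1 - 0.0027)^260 = 50%.

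**Step 2: no change, Poisson counts, limits estimated from 12 months, 3-sigma rule only.** In simulation, each practice signals with probability 0.034, 0.030 and 0.025 at means of 8, 20 and 40 a month over 6 months. Over 13 months the values are 0.073, 0.060 and 0.055. With 1 - (1 - p)^10, at least one of 10 POC practices signals in 29%, 26% and 22% of trials over 6 months, and in 53%, 46% and 43% over 13.

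**Step 3: no change, with run rules.** Take 3-sigma, 8 points on one side and a 6-point trend, means of 10 to 40 a month, and limits from either a Poisson count chart or an individuals chart. Runs may begin in the baseline months.
- 6 study months: p is about 0.055 to 0.123, so 1 - 0.945^10 = 43% to 1 - 0.877^10 = 73%.
- 12 study months: p is about 0.133 to 0.233, so 1 - 0.867^10 = 76% to 1 - 0.767^10 = 93%.

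Extra-Poisson variation raises the rate on a Poisson count chart. With a CV of 0.2 and the 3-sigma rule alone, p over 6 months becomes 0.089, 0.172 and 0.353 at means of 8, 20 and 40.

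**Step 4: the same change in every practice, so no arm difference.** Expected signalling practices per arm of 10, at means of 8 / 20 / 40 a month on a Poisson count chart. The run rules here are 2-of-3, 4-of-5 and 8 on one side.

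| Common change | Study months | 3-sigma only | With run rules |
|---|---|---|---|
| +30% | 6 | 2.4 / 4.1 / 6.6 | 4.3 / 7.0 / 9.1 |
| +30% | 13 | 4.2 / 6.4 / 8.7 | 7.1 / 9.3 / 9.9 |
| -30% | 6 | 0.0 / 1.1 / 4.4 | 3.2 / 6.9 / 9.4 |
| -30% | 13 | 0.1 / 2.1 / 6.7 | 6.8 / 9.4 / 10.0 |

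These expectations are the same in both arms, so a signal in a POC practice carries no information about the device. A fall at low counts can go unseen under the 3-sigma rule alone.

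**Step 5: what a between-arm comparison does.** Suppose each practice signals with the same probability in both arms, anywhere from 0.05 to 0.9. Fisher's exact test of 10 against 10 practices (two-sided 0.05) then declares a difference in at most about 1.2% of trials. At least one POC practice still signals in 1 - 0.95^10 = 40% of trials at probability 0.05, and in 1 - 0.7^10 = 97% at 0.3.

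**The case against.** A reader might infer that section 7.2.3 treats every signal, and every change shared by both arms, as an effect of the study. The text does not support that. It names the PHO as an alternative source, charts laboratory practices beside POC practices, and nowhere says that one signalling practice is enough. The criterion of at least one POC practice signalling is mine, used to show scale.

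Nor are the charts the only safeguard against novelty. Section 7.2.2 plans a time series analysis of device use and a sensitivity analysis on the later period. The charts are neither a primary nor a secondary outcome, and the overview gives them a descriptive role.

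The Hawthorne effect is a sound objection to relying on an arm contrast alone. Both arms are in the study, so such an effect may appear in both, and an arm-by-period term would cancel it. A rule that nothing counts unless it differs between arms would discard something the section wants to examine. An arm contrast is right for device effects only.

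The inputs are also open to challenge. One chart per practice is the natural reading but not explicit. The 30% change is illustrative. The acceleration described in section 7.1 had largely happened by April 2014, with about 80% screened. It therefore lies in the baseline months, and a fall during the study is as plausible as a rise.

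All of this limits the point without removing it. The sentence still assigns association to a rule that cannot assess it.

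**Conclusion.** The point holds in limited form. Shewhart criteria can detect special cause variation in these series. They cannot determine its association with the device or the PHO, and that follows from their definition, whatever the counts.

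The size depends on assumptions. With one chart per practice, 10 to 40 assessments a month, 12 baseline months and the step 3 rules, at least one of 10 POC practices signals with no change in about 43-73% of trials over 6 months and 76-93% over 12. With the 3-sigma rule alone the figures are lower, 22-29% over 6 months. A change common to both arms yields the same expected number of signals in each.

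The consequence is confined to how the charts are interpreted. The non-inferiority and superiority conclusions rest on section 7.2.2 and do not change. The wording should be corrected before the charts are used to explain results.

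**What to change.** In section 7.2.3:

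- Use Shewhart criteria only to detect special cause variation, and label the charts descriptive.
- Assess any POC effect (novelty, teething difficulties, work process) by a POC-versus-laboratory contrast. One suitable form is a practice-by-month count model with practice random effects, calendar month and an arm-by-period term (prior, early study, later study), reported with its 95% CI.
- Report a change common to both arms separately, as compatible with either a Hawthorne effect or outside causes such as the national target. Do not attribute it to the device.
- If association with the PHO is to be kept, state a comparison between PHOs over the same periods and call it observational, since PHO is not randomised.

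The cost is a change of wording and one additional model on data already being extracted. With 20 practices the contrast will be imprecise, so the conclusion about novelty may be less definite.

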### 7.2.4 *Cost analysis*

A cost analysis will be performed for both groups based on practice consultations and testing for lipids and diabetes (laboratory or POC) from a payer perspective. Data on numbers of practice consultations, laboratory and POC device tests will be sourced from PREDICT. Unit cost data will be obtained from the PHOs, local laboratories and Roche Diagnostics. Qualitative information on other practice resource use will be collected through the practice follow-up. Practice staff costs will be assessed by asking practices about the amount of nurse and GP time required under POC and laboratory testing.

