### 3.3 Assessment of cholesterol and diabetes

As part of a CVD risk assessment, the New Zealand guidelines recommend blood lipid testing and use of the ratio of total cholesterol to high density lipoprotein (TC/HDL, fasting or non-fasting) in the risk calculation. In 2009, screening for diabetes was also recommended as part of the risk assessment using either fasting glucose or haemoglobin type A1c (HbA1c, fasting or non-fasting).

Currently, if the lipid and diabetes values are not known at the visit, the GP or practice nurse must order a blood test (via a laboratory referral form). Transmission from the screen to the PREDICT server will not occur unless all the data fields are filled in. If screening blood tests are not available the assessment can be "parked" and saved until all data is subsequently available. Ideally then a risk assessment would be completed with the patient on a second visit. It is not known what proportion of risk assessments remain incomplete due to the laboratory testing step and necessity for two consultations.

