## 6.7 Withdrawal criteria

Patients will receive CVD risk assessment as part of normal clinical care which includes testing for lipids and diabetes. For patients in the POC group, a laboratory test may be requested by the health care practitioner or participant, instead of, or in addition to, point-of-care testing. This will not withdraw the patient from the study.

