### 6.12.3 *Qualitative assessment of practice acceptability*

The qualitative assessment (practice questionnaire) will collect information from practices allocated to the POC group on where the POC testing was done, who did it, how user friendly was the tool, how user friendly was the integration with the PREDICT CVD risk assessment, what extra time and resources were required, what changes in work flow were required, any teething difficulties or issues arising during the time period, and potential opportunity costs imposed by having the Cobas b 101 device in the practice.

A short questionnaire will also be administered to the control practices asking about current practice for obtaining HbA1c and TC/HDL blood results, the major barriers to CVD risk assessment in their practice and their perceptions about the acceptability and feasibility of having the cobas b 101 device in the practice.

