### 10.3 Supply records

Supply records of the Cobas b 101 device and consumables will be kept by Roche Diagnostics NZ Ltd. These will be provided to the study investigators on request.

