### **13.3 Case report form procedures**

The practice questionnaires will be completed by practices allocated to the POC group at the time of the end of study practice visits. Practices will be identified by a study identification number. Information from the questionnaires will be entered into an excel spreadsheet by the researcher.

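### The cost analysis takes every test and consultation count from PREDICT, an assessment record with no described place for quality-control discs and no clear one for repeat or duplicate tests

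*Protocol*

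**What the plan says.** Section 7.2.4 costs "practice consultations and testing for lipids and diabetes (laboratory or POC) from a payer perspective". Its source for quantities is a single system: "Data on numbers of practice consultations, laboratory and POC device tests will be sourced from PREDICT". Unit costs come from the PHOs, local laboratories and the manufacturer. Other practice resource use is gathered qualitatively at practice follow-up, and practices are to be asked about nurse and GP time under both kinds of testing.

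Several other sections bear on whether PREDICT can supply those counts:

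- Section 3.3 on what reaches the server: "Transmission from the screen to the PREDICT server will not occur unless all the data fields are filled in". Section 6.12.2 says investigators receive data on patients with a completed or parked assessment, and 7.2.5 defines a parked one as lacking only its laboratory values.
- Section 6.7, on the POC group: "a laboratory test may be requested by the health care practitioner or participant, instead of, or in addition to, point-of-care testing".
- Appendix 4, item 2, requires acceptance testing of new batches, monthly internal quality control in the practices, and extra control runs after certain events.
- Section 10.3: "Supply records of the Cobas b 101 device and consumables will be kept by Roche Diagnostics NZ Ltd". They are available to the investigators on request, but 7.2.4 does not use them.
- Section 6.12.3 gives control practices a short questionnaire "asking about current practice for obtaining HbA1c and TC/HDL blood results", together with barriers to assessment and views on the device. Section 13.3, however, says: "The practice questionnaires will be completed by practices allocated to the POC group".

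**The concern.** A cost analysis needs a count of resources used. A system that stores assessments counts something else: how many templates were submitted or left waiting for blood results. The two differ wherever a disc, a laboratory test or a visit leaves no trace in an assessment. For the POC arm the clearest case is quality control, which the protocol itself requires and which uses discs without a patient.

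The cost comparison is a listed secondary objective (section 5), and section 4 presents it as the first of its kind in New Zealand primary care. If its quantities are incomplete by an unknown amount in each arm, the cost difference cannot be interpreted with confidence, even with correct unit costs. The same applies to staff time if laboratory-arm time is not collected from laboratory-arm practices.

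**Working it through.** The plan states no cost figure to reproduce. The check is whether each resource has a described route into PREDICT, and how large the clearest omission could be.

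**Step 1. Routes into the count**

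| Resource | Where the protocol provides for it | Route into PREDICT |
|---|---|---|
| Patient test leading to a completed assessment | 3.2, 3.3 | Yes, as a result value in the template |
| Monthly and event-driven control discs, batch-acceptance discs | Appendix 4, item 2 | None described; no patient or template is involved |
| Repeat disc for the same patient | Not addressed | None described |
| Laboratory test added to a POC test | 6.7 | Not clear; no second result field is described |
| Laboratory test never entered in a completed assessment | 3.3, 7.2.5 | Not clear; a parked template is one without laboratory values |
| Separate visits for one assessment | 3.3 (ideally a second visit) | No visit count described |

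The follow-up table in 6.12.3 does list laboratory and Cobas b 101 data under PREDICT at end of study. It does not say whether this means one value per assessment or every test run.

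**Step 2. Size of the quality-control part, per analyte**

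Inputs from Table 4 (section 10.1): 198 boxes of 10 discs and 120 control packs of 2 vials, the same for HbA1c and for lipids.

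- Discs supplied: 198 × 10 = 1,980.
- Control vials supplied: 120 × 2 = 240, or 12 packs for each of 10 practices.
- If every vial is run once, at one disc per vial (assumption; the protocol gives no such figure): 240 / 1,980 = 12.1%.

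**Step 3. Sensitivity**

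Routine control discs = practices × months × control levels per run, at one disc per level. The number of levels is assumed to be 1 or 2. Duration is 3 to 6 months in sections 1 and 6.11, but 12 months in the primary aim. The share is taken first of all 1,980 discs, then of the discs run if there were 500 patient tests (10 practices × 50).

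| Months, levels | Control discs | Share of 1,980 | Share if 500 patient tests |
|---|---|---|---|
| 3, 1 | 10 × 3 × 1 = 30 | 1.5% | 30/530 = 5.7% |
| 6, 2 | 10 × 6 × 2 = 120 | 6.1% | 120/620 = 19.4% |
| 12, 1 | 10 × 12 × 1 = 120 | 6.1% | 120/620 = 19.4% |
| 12, 2 | 10 × 12 × 2 = 240 | 12.1% | 240/740 = 32.4% |

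Event-driven control runs, batch acceptance and repeats would add to these. The protocol gives no rate for any of them.

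**Step 4. Staff time**

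Section 7.2.4 needs nurse and GP time under laboratory testing. In 6.12.3 the POC questionnaire topics include extra time and resources, while the control topics include no time item. Section 13.3 mentions only POC practices as completing questionnaires, which does not fit 6.12.3.

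**The case against.** PREDICT is not shown to be without test data. The follow-up table places laboratory and device data there, so repeats or duplicates might appear in an extract that the protocol does not define. This stands for repeats and duplicates. It does not help with control runs, which have no patient record.

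PREDICT is also not the only input. Facilitators document additional staff time and other resources at follow-up (6.11), and 7.2.4 commits to asking practices about time. That route is qualitative apart from time, and it gives no disc count. The listed topics in 6.12.3 are a summary rather than an item list, and 13.3 does not say that control practices are excluded; the two sections need aligning, but they do not prove that laboratory-arm time will go uncollected.

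A reader might infer that the comparison is biased in favour of the device. The documents do not support this. Second visits and laboratory tests that never reach an assessment belong mainly to the laboratory pathway, and missing them understates laboratory cost. Nor is it stated whether the manufacturer's unit cost already includes controls, or whether the payer bears them.

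A reader might also divide supply by planned assessments: 1,980 / 500 = 3.96 discs per assessment, so that (1,980 − 500) / 1,980 = 75% would go uncounted. That does not follow. The study continues until at least 1,000 assessments are done and "all the point of care consumables have been utilised by the POC group", so assessments may exceed the minimum. After 240 control discs, 1,980 − 500 − 240 = 1,240 discs would still need an explanation, and the protocol offers none.

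Finally, detailed costing sources are often left to an analysis plan. Here, though, the protocol itself names the source.

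**Conclusion.** The point holds in limited form. Followed as written, 7.2.4 would likely undercount POC consumables: control and batch-acceptance discs have no described route into PREDICT, and repeat discs and added laboratory tests have no clear one. The quality-control part is about 12% of discs supplied if all 240 vials per analyte are run at one disc each. Under the assumptions shown, routine control runs range from 1.5% to 12% of full supply, or 6% to 32% of discs run if there were only 500 patient tests. These are shares of discs, not of cost; the protocol gives no unit costs.

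The net direction of bias between arms is not established. What can be said is that the quantities are incomplete to an unknown degree in both arms. This concerns a secondary outcome and leaves the primary analysis untouched.

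**What to change.** In 7.2.4:

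- Take disc, control and lancet quantities per POC practice from the supply records (10.3), less unused stock at study end. Leave out the additional consumables that 10.1 says are supplied for training.
- Separate control and repeat use from patient tests, so that discs not used for an assessment are not charged as if they were. The quality-control data overseen under Appendix 4, item 4, are a natural source for the control runs.
- State how quality-control cost enters the payer-perspective cost.
- Use PREDICT for the numbers of completed and parked assessments, and define the laboratory and device data that the follow-up table expects from it.
- Where the local laboratories can supply practice-level test counts, use them as a cross-check in both arms.

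In 6.12.3, add a nurse and GP time item to the control-practice questionnaire. Reword 13.3 so that both arms complete one.

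The cost is modest: a request for records already available, a stock count, a laboratory query, one questionnaire item and some wording. The protocol version is dated 30 March 2015 and the estimated study end is June 2015, so the end-of-study questionnaire could still be changed. The downside is that the POC cost may look less favourable.
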